### Details of intervention:

A detailed history and examination will be gathered from the already available information of the patient in the admission records at hospital. The patients randomised into experimental group will be interrogated by the homoeopathic physician only for the additional information required from Homoeopathy perspective.

As per each case, individualized homoeopathic medicine will be prescribed. Symptomatic Homoeopathy management of Suspected and Diagnosed cases of Mucormycosis has been advised in Guidelines by Ministry of AYUSH.^[[69]](#endnote-69)^ These guidelines will play a vital role in identification of the indicated medicines in this proposed study.

Daily recording of the administered dose will be recorded and also captured in the Case Record Form (CRF) developed by the Homoeopathy team, which will be having content other than, and in addition to the standard form, which will be filled at the hospital. If there is any change in dosage / prescription of medications during the study period, that will be mentioned with reason in the prescription chart. If these medicines are stopped, that too would be recorded with reason.

The patients assigned to the placebo group will be given placebo in the form of similar looking homoeopathic pills of 30 size, dispensed with the 30% V/V dispensing alcohol.

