| **Inclusion Criteria** | - Stage 1 and 2 (Staging document annexed) of ROCM - Age > 18 years - All genders - Fungal smear analysis through KOH staining/ microscopy of affected area showing presence of mucormycetes (to save precious time), followed by following exploratory imaging techniques:   - CEMRI (for ruling out Stages 3 and 4)   - CT-guided endoscopy-cum-biopsy (for detailed histopathology study) |
| **Exclusion Criteria** | - ROCM cases in stages 3 and 4(Staging document annexed) presenting with bony erosion, cerebral vascular invasion, invasion into the cranium, orbital apex or cribriform plate of the ethmoid bone, cavernous sinus (II-VI cranial nerve palsies) will be excluded. - Diagnosed cases of Pulmonary ,Cutaneous, Gastrointestinal ,Advanced, disseminated mucormycosis will be excluded. - Pregnant and lactating women. - In the opinion of the clinical team, progression to death is imminent and inevitable within the next 24 hours, irrespective of the provision of treatments. |
| **Follow-up period** | - Patient will be assessed clinically twice a day; MRI/endoscopy-cum-biopsy will be assessed on day 1, 14 and 28. |
| **Outcomes** | **Primary Outcome**   1. Change in condition as seen in standard imaging or other diagnostic techniques:  - MRI contrast in ROCM cases   **Secondary Outcomes**   1. To assess difference in the survival of the patients in both the groups during hospitalization. |
| **Endpoint** | - Recovery as per the outcome parameters, followed by discharge from hospital - Advanced, disseminated mucormycosis - Death of the patient |
| **Study Product, Dose, Route** | - Individualized homoeopathic medicine in appropriate dose, orally, four times daily; or more frequently in severe cases. |
| Placebo | Placebo group patients will receive identical placebo (globules moistened with dispensing alcohol) as an add on to standard protocol treatment. Dose repetition will be a in similar pattern to medicine group. |
| Duration of administration | Maximum 28 days (depending on the patient’s admission duration) |
| Statistical Methodology | All primary efficacy analyses will be conducted in the Intention-to-treat (ITT) population; thus, all randomized patients should be included in the primary analysis. |
| Funding Agency | Central Council for Research in Homoeopathy, Ministry of AYUSH, Govt. of India |
| Budget | Rs. 75 lakhs approx. |

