# Material & Methods

## 3.1 STUDY DESIGN

Study design is single blind, randomized clinical trial.

Of the 2 groups running in parallel, the control arm will receive conventional treatment as per IMP, while the other group will receive homoeopathic intervention along with IMP. Allocation ratio will be 1:1 through randomisation obtained from computerised random number generator.

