### Change of prescription

The prescribed medicine will be changed if no change in the next scheduled laboratory investigations or patient reports to be clinically unwell, even after at least 3 doses of the prescribed medicine.

**In either arm, no patient will be devoid of the conventional management as per IMP at any given point of time**. The allopathic medicines given during the study duration will be recorded specifically, with details of reason for administration, the name of the medicine with dose, along with any other relevant details, in the daily medication sheet as well as the CRF. The participants of the allopathy arm will get non-medicated, similar looking lactose globules, as placebos.

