## LABORATORY INVESTIGATIONS

| **INVESTIGATIONS** | | |
| --- | --- | --- |
| - **Lab parameters** | CBC, ESR, FBS, PPBS, HbA1C, LFT, KFT with electrolytes | D0 and as per IMP |
| - **Imaging technique** | - CEMRI of Brain with orbits and sinuses. | - (Only at inclusion) |
|  | - CEMRI PNS | - D0 (or latest report if it is within 03 days of enrolment day), D14 and D28, or before or after as per IMP/ requirement |
|  | - CT guided endoscopy-cum-biopsy Fungal smear/KOH staining | - As per IMP, if required |

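### The protocol masks only the patient: nothing masks the team giving conventional care, and the homoeopathic interview and prescription changes, described for the active arm alone, could reveal the allocation

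*Protocol*

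**What the plan says.** **Masking.** Section 3.1 of the protocol states: "Study design is single blind, randomized clinical trial". It does not say who is blinded. The only masking device described is the placebo. The synopsis says "Placebo group patients will receive identical placebo (globules moistened with dispensing alcohol) as an add on to standard protocol treatment", with doses repeated in a similar pattern to the medicine group. Section 3.4 twice describes look-alike globules.

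**Homoeopathic contact.** Under Details of intervention in 3.4: "The patients randomised into experimental group will be interrogated by the homoeopathic physician only for the additional information required" from the homoeopathic perspective. No interview is described for placebo patients.

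**Prescription changes.** The same section says of "any change in dosage / prescription of medications during the study period, that will be mentioned with reason in the prescription chart". Stopping is recorded with its reason too. Under Change of prescription, "The prescribed medicine will be changed if no change in the next scheduled laboratory investigations" or if the patient remains unwell. No counterpart is given for placebo.

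**Conventional care.** "In either arm, no patient will be devoid of the conventional management as per IMP at any given point of time". The protocol text at hand does not give the content of the IMP. Conventional medicines are to be recorded with reason, name and dose in the daily medication sheet and the CRF.

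**Scan timing.** The Laboratory investigations table sets the sinus MRI at baseline, day 14 and day 28, "or before or after as per IMP/ requirement". Change on contrast MRI is the primary outcome (section 3.6).

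**The concern.** The comparison is meant to isolate the adjuvant, with conventional care equal apart from chance. That holds only if the people who deliver the care, or decide when to scan, do not act on knowledge of the arm. If they learn the arm and treat patients differently, the difference in treatment is real and appears on the MRI. Masking the patient does not stop this, and masking the MRI reader would not either, because the reader would be scoring a true difference. The effect of the co-treatment would then be credited to the adjuvant, or would hide an effect of it. The analysis described in the protocol has no step that would separate the two. Masking and record handling have to be settled before enrolment, because analysis cannot restore them.

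**Working it through.** **1. The text, set side by side**

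| Feature | Active arm | Placebo arm |
| --- | --- | --- |
| Globules | Individualised medicine | Look-alike globules |
| Repetition of doses | Four times daily or more often | Similar pattern |
| Homoeopathic interview | Described | Not described |
| Change of prescription when there is no response | Described, reason recorded | Not described |
| Conventional care | As per IMP | As per IMP |
| Recording of conventional medicines | Yes | Yes |
| Masking of the team giving IMP care | Not stated | Not stated |

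The globules and dose pattern match between arms. The interview and the change-of-prescription step do not. Either could show ward staff which arm a patient is in: the interview because it takes place with an inpatient, and the prescription change if the chart is open to them. MRI dates can move, so scan timing is one concrete place where knowledge of the arm could act. Conventional care is another, to whatever extent the IMP leaves latitude.

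**2. Size: inputs**

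The protocol gives no figure for this bias. It does give 36 per arm (synopsis), a 5% type I error and a planned difference of 0.10 (Target sample size). The following are assumptions: no true effect, a binary response, response rates centred on 50%, and a shift d in favour of one arm caused only by co-treatment.

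**3. Exact calculation**

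The responders in the two arms are X ~ Bin(36, 0.5 − d/2) and Y ~ Bin(36, 0.5 + d/2). All 37 × 37 outcomes are enumerated. The test is the uncorrected chi-square at two-sided 0.05, that is z = (Y − X)/36 ÷ √[p̄(1 − p̄)·2/36] with |z| > 1.96.

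| Shift d | Significant for favoured arm | Significant for other arm | Either |
| --- | --- | --- | --- |
| 0 | 2.3% | 2.3% | 4.5% |
| 0.05 | 5.7% | 0.8% | 6.5% |
| 0.10 | 12.4% | 0.2% | 12.6% |

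Each total is taken from unrounded values.

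**4. What imbalance would produce such shifts**

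If an effective conventional measure is used e more often in one arm and raises response by g, the spurious difference is d = e × g. With assumed e from 0.10 to 0.30 and g from 0.20 to 0.40:

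- smallest: 0.10 × 0.20 = 0.02
- largest: 0.30 × 0.40 = 0.12

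The two-sided rejection rate by the normal approximation is Φ[(d − 1.96·s0)/s1] + Φ[(−d − 1.96·s0)/s1]. For d = 0.12 on a 50% base:

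- p̄ = 0.56
- s0 = √(0.56 × 0.44 × 2/36) = 0.117
- s1 = √[(0.50 × 0.50 + 0.62 × 0.38)/36] = 0.116
- rejection rate = 17.5%

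For d = 0.02 it is 5.3%. On an assumed 80% base the range is 5.5% to 30.9%. Small imbalances barely matter. Large ones yield a spurious difference about as big as the planned 0.10.

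**The case against.** The strongest objection is that the protocol does not show the hospital team to be unmasked or the chart to be theirs.

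- **The chart.** The chart sentence follows the description of a CRF developed by the homoeopathy team. Conventional medicines go to a separately named daily medication sheet. Data collection methods lists prescription decisions among the homoeopathy data. A chart held by the homoeopathy team is at least as natural a reading. This stands: a reader might infer that any clinician opening the chart can identify the arm, but the text does not say so. What remains is that access is not restricted.
- **Who decides.** A reader might also infer that an unmasked team has free discretion over surgery, antifungals and discharge. No section says who decides these. Surgery appears only in the background, the latitude left by the IMP cannot be judged, and the synopsis ties discharge to recovery on the outcome parameters. This stands too.
- **Safeguards.** Both arms receive IMP care, placebo repetition is matched, and conventional medicines are recorded with reasons. An imbalance in medicines could therefore be seen and reported. This stands in part: recording detects and does not prevent, and the rule names medicines, not procedures or scan timing.
- **Magnitude.** The 50% rate and the shifts are assumptions, the primary outcome is not defined as binary, and nothing shows which arm would be favoured. Counting both directions, a 5-point shift moves rejection only from 4.5% to 6.5%. All of this stands, so the figures show scale only.

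**Conclusion.** The point holds as a gap in the design. Single blind with look-alike globules masks the patient and does not imply that the team giving conventional care is masked. The active arm has an interview and a prescription-change step for which no placebo counterpart is described. Knowledge of the arm could therefore reach conventional care and MRI timing, and so the primary outcome.

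The documents do not support the stronger statement that the hospital team is unblinded, or that co-treatment will differ. They say neither who is masked nor who reads the prescription chart.

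The size cannot be derived from the protocol. On an assumed 50% response, no true effect and a 5- to 10-point shift, the favoured-direction false-positive rate at 36 per arm rises from 2.3% to between 5.7% and 12.4%. With a small imbalance the effect is minor. The change is still worth making before enrolment, because it costs little and cannot be made afterwards.

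**What to change.** 1. **Section 3.1:** state that the patient and the team applying the IMP and deciding scan timing and discharge are masked, and that only the homoeopathic prescriber and dispenser know the arm.
2. **Section 3.4, Details of intervention:** keep medicine names, changes and reasons in the homoeopathy CRF only, and say who may see it. Any ward chart carries the same coded study-globules entry in both arms.
3. **Section 3.4, interview and Change of prescription:** have the existing homoeopathic physicians carry out the same case-taking and prescription-review contact in both arms, for example by taking the case before randomisation. Changing the chart wording alone would leave the experimental-group interview as a cue.
4. **Statistical methods:** report conventional co-treatment by arm, using the records already planned.

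Look-alike globules and a separate homoeopathy CRF already exist. The cost is some extra interview time for existing staff, coded labels and an emergency code-break route. No dose or clinical rule changes.

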### Change of prescription

The prescribed medicine will be changed if no change in the next scheduled laboratory investigations or patient reports to be clinically unwell, even after at least 3 doses of the prescribed medicine.

**In either arm, no patient will be devoid of the conventional management as per IMP at any given point of time**. The allopathic medicines given during the study duration will be recorded specifically, with details of reason for administration, the name of the medicine with dose, along with any other relevant details, in the daily medication sheet as well as the CRF. The participants of the allopathy arm will get non-medicated, similar looking lactose globules, as placebos.

### Duration of intervention:

28 days. However, if patient is discharged before, the medicines will continue, if needed, and the follow up will be done telephonically on the 14^th^ and 28^th^ day of illness.

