## 3.6 OUTCOMES

#### Primary:

Change in condition as seen in standard imaging or other diagnostic techniques:

- MRI contrast in ROCM cases

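### Early discharge leads to telephone follow-up while the primary MRI is due at D14 and D28 with no window, so the primary measurement can be missing or mistimed in patients who recover

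*Protocol*

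**What the plan says.** - **Primary outcome (section 3.6):** "Change in condition as seen in standard imaging or other diagnostic techniques", specified as "MRI contrast in ROCM cases". No assessment day is named.
- **Scan schedule in the synopsis (Follow-up period):** "MRI/endoscopy-cum-biopsy will be assessed on day 1, 14 and 28". No flexibility is mentioned.
- **Scan schedule in the Laboratory Investigations table:** contrast MRI of the paranasal sinuses at "D0 (or latest report if it is within 03 days of enrolment day), D14 and D28, or before or after as per IMP/ requirement". The wider scan of brain, orbits and sinuses is marked "Only at inclusion".
- **After early discharge (section 3.4, Duration of intervention):** "However, if patient is discharged before, the medicines will continue, if needed, and the follow up will be done telephonically". The calls fall on the 14th and 28th day, counted by illness.
- **Withdrawal (section 3.5):** a patient whose disease extends past the eligible stages is withdrawn. Nothing is said about a scan at or after that point.
- **Analysis set (synopsis and Statistical Methods):** intention to treat, with every randomised patient in the primary analysis.

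**The concern.** The only contact described after discharge is a telephone call, and a call cannot produce an MRI. Recovery followed by discharge is itself a listed endpoint in the synopsis, so going home early is a mark of success. A site that follows section 3.4 literally would not obtain the primary measurement in patients who do well. At the other end, section 3.5 takes out patients who progress. Both losses would depend on the outcome. If the arms differ in how fast patients go home or progress, a comparison of scanned patients no longer compares the randomised groups.

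The open timing raises a related problem. A scan that may be brought forward or put back according to clinical need is taken at a moment chosen by the patient's course, so change from baseline is measured over different intervals in different patients.

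A statistical analysis plan can say how missing scans are handled. It cannot recover scans that were never taken, so the collection rule has to be settled in the protocol.

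**Working it through.** The protocol gives no figure for discharge, progression or missing scans, so there is none to reproduce. The point rests on reading the sections against each other; the arithmetic only shows how much could be at stake.

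**Step 1. The sections side by side**

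| Item | Synopsis | Investigations table | Section 3.4 |
|---|---|---|---|
| Mode | MRI/endoscopy with biopsy | Contrast MRI of sinuses | Telephone, if discharged early |
| Timing | Days 14 and 28, fixed | D14 and D28, movable, no window | 14th and 28th day |
| Clock | Starts at day 1 | Starts at D0, tied to enrolment | Day of illness |

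The clocks are not interchangeable. If enrolment (D0) falls on illness day k, illness day 28 is study day 28 − k. The call and the scan that share a day number therefore fall on different dates unless k = 0.

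**Step 2. Scan field**

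The sinus scan is scheduled at D0, D14 and D28, so change within the sinuses is measured like for like. Annexure 1 defines Stage 3 as orbital and Stage 4 as central nervous system involvement. The only scheduled scan stated to cover those sites is done at inclusion, and no section ties such spread to the primary outcome.

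**Step 3. Possible size (all rates assumed)**

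From the document: 36 per arm (synopsis) and a design difference of 0.10 (Target Sample Size).

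*Bounds.* If a share m of each arm has no scan, each arm's success proportion is known only to within m, and the difference only to within 2m.
- m = 0.10: 2 × 0.10 = 0.20
- m = 0.30: 2 × 0.30 = 0.60

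*Direction.* Let S be true success, d the share who are early-discharged successes without a scan, and g the share who progress and have no scan. Success among the scanned is (S − d)/(1 − d − g). Take S = 0.70 (adjuvant) v 0.60 (control), a true gap of 10 points.

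| Case | d | g | Adjuvant | Control | Gap (points) |
|---|---|---|---|---|---|
| A | 0.40 v 0.30 | 0 | 0.30/0.60 = 50.0% | 0.30/0.70 = 42.9% | +7.1 |
| B | 0.40 v 0.30 | 0.15 v 0.20 | 0.30/0.45 = 66.7% | 0.30/0.50 = 60.0% | +6.7 |
| C | 0.50 v 0.30 | 0 | 0.20/0.50 = 40.0% | 0.30/0.70 = 42.9% | −2.9 |
| D | 0.50 v 0.30 | 0.15 v 0.20 | 0.20/0.35 = 57.1% | 0.30/0.50 = 60.0% | −2.9 |

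In case A about 22 (36 × 0.60) and 25 (36 × 0.70) patients are scanned.

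*A milder case.* Take improvement of 60% v 50% and progression of 15% v 20%, with half of the improved and all of the progressed unscanned. The scanned share is 0.30 + 0.25 = 0.55 in the adjuvant arm and 0.25 + 0.30 = 0.55 in the control arm. Observed improvement is 0.30/0.55 = 54.5% v 0.25/0.55 = 45.5%, a gap of 9.1 points against a true 10.

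The distortion thus runs from slight to a change of sign, depending on rates the protocol does not give.

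**The case against.** Several objections have force.

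- **A reader might infer that the scan is cancelled at discharge.** No section says so. The telephone sentence stands under the duration of intervention, and neither the synopsis nor the investigations table limits D14 and D28 imaging to inpatients. This stands: the text shows an unresolved conflict, so the scan can be missing, not that it will be.
- **A reader might infer that baseline and follow-up scans cover different fields.** For the sinuses they do not, because the sinus scan is also done at D0. The field point is confined to orbital and central nervous system spread.
- **Such spread is not left unseen.** Patients are assessed clinically twice a day, advanced disseminated disease and death are listed endpoints, section 3.5 responds to progression, and extra scans are permitted as required. This stands too. What remains is that the progression is not linked to the primary outcome.
- **Flexible timing could help.** A scan brought forward could be taken just before discharge and so reduce missing data. True, but nothing requires this, and such a scan would be timed by recovery.
- **The illustrations are selective.** They assume that every early discharge counted is an unscanned success, that D28 is the primary day although section 3.6 names none, and that only scanned patients are analysed although the plan requires all randomised patients. A patient discharged after D14 could already have that scan. The change of sign needs a 20-point difference in early discharge, twice the assumed effect.

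**Conclusion.** The concern holds in limited form. Section 3.4, the synopsis and the investigations table conflict on mode, timing and day count, and no section provides a scan after discharge or withdrawal. The primary measurement can therefore be missing, or taken at outcome-dependent times, in patients who recover and go home. Section 3.5 adds the same risk for patients who progress. Both sit badly with the commitment to analyse everyone randomised.

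The size cannot be fixed from the document. At an assumed 10% unscanned per arm, the bounds on the difference are already twice as wide as the design difference of 0.10 (0.20/0.10 = 2). A reversal of the result is only an extreme assumed case (40.0% v 42.9%, or 57.1% v 60.0% with unscanned progressors); the milder case left the gap almost unchanged, at 9.1 points. The documents do not support saying that the outcome is lost in all such patients or that sinus scans are not comparable over time.

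**What to change.** 1. Reconcile the synopsis, sections 3.4 and 3.5 and the investigations table on one day count from randomisation.
2. State that the already scheduled D14 and D28 sinus MRI is obtained in every surviving randomised patient: at an outpatient visit if discharged and, where consent allows, also after withdrawal from treatment.
3. Set a fixed window, for example ±3 days. Clinically triggered scans are additional and do not replace the scheduled ones.
4. Count documented Stage 3 or 4 disease as failure in the primary outcome. This deals with spread outside the sinuses without a wider follow-up scan.

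These changes concern outcome collection and definition only, not how patients are treated or when treatment stops. The cost is protocol wording and return visits for discharged patients; the scans are already in the schedule.
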